### Interim analyses {21b}

Interim analysis is not provided.

### Methods for additional analyses (e.g., subgroup analyses) {20b}

No subgroup analyses are planned.

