### Objectives {7}

The main objective of our study is to test the hypothesis that a higher expectation for the efficacy of TMS treatment leads to a better therapy success regarding the intensity of the depressive disorder. In this, we do not seek to investigate the efficacy of TMS in MDD per se, but rather the effects of treatment-related expectation. In order to realize this, the intervention as a more positive and comprehensive patient education aims to induce higher expectations, which, in the next step, is assumed to lead to a better outcome. Therapy success will be evaluated by means of psychometric tests and cognitive tasks. We further intend to explore a possible normalization of inflammatory parameters as an additional outcome parameter.

Furthermore, in an exploratory approach, the aim is to identify predictors of the expectancy effect in imaging, at the level of both biological and psychological parameters. Predictors of expectancy effects in functional connectivity in the rs activity in the DMN as well as in cognitive and emotional networks are to be identified. We also believe that CAR in saliva can be considered as a predictor of expectancy effects.

Another goal of our study is to investigate the role of the cerebellum in depression and expectancy effects: we hypothesize that mild cerebellar symptoms as well as a limitation in the acquisition of conditioned blink reflex responses (a cerebellum-dependent learning paradigm) can be detected in a subset of patients. Our hypothesis is that the expectancy effect is less pronounced in this group of patients, which is also reflected in the altered functional connectivity of the cerebellum.

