### Trial design {8}

We are planning an interventional, monocentric, randomized, controlled trial with two MDD patient groups of 30 participants each.

Our study is of the parallel group type, i.e., we are looking at two groups of patients in parallel, with one group of patients receiving an intervention while the other one does not. The framework is “superiority”: we expect to see superiority in outcome parameters in the intervention group. The allocation ratio in the intervention versus the control group is 30:30.

As it is to be expected that about 10% of the data will be lost due to the complex study protocol with several examinations at a total of four time points, at least 35 patients should be recruited per group. This minimum recruitment number seems achievable based on our experience with previous studies. The details of the intervention are outlined below.

In addition, an age-, sex-, and education-matched control group of 30 participants will be recruited, who will serve as a control only for the additional experimental investigations, which is the MRI part and the eyeblink conditioning. In these two subprojects, the first step is to evaluate the changes in the context of depressive illness in general compared to a healthy control group, see the “Outcomes {12}” section.

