Blood sampling: In total, less than 60 ml of blood will be taken. Plasma concentrations of C-reactive protein (CRP), interleukin (IL)-6, and tumor necrosis factor (TNF)-α as systemic inflammatory markers will be determined along with (epi)-genetic markers, e.g., acetylations.

Collection of saliva: Saliva samples will be self-collected by the study participants with commercial collection devices. This is a painless procedure that usually takes 60 s. The salivary cortisol awakening response will be used as a measure of the activity of the hypothalamic–pituitary–adrenal (HPA) axis. Hormone determinations will require three saliva samples taken on each of two consecutive days immediately, 30 and 45 min after awakening.

Parameters indicative of cerebellar dysfunction: survey at one time point before therapy (neurological examination and ataxia scores, see below).

Eyeblink conditioning: Delay conditioning paradigm will be used [16]. A tone will be used as the conditioned stimulus (CS) and an air puff directed to the outer canthus of the eye as the unconditioned stimulus (US). CS and US coterminate. Surface EMG recording of the orbicularis oculi muscles will be used to measure unconditioned (UR) and conditioned (CR) responses. The focus will be on the acquisition of conditioned blink reflex responses [16, 18]. Participants learn that the CS predicts the occurrence of the US and learn to close their eyes prior to the occurrence of the US. The CR incidence is the primary outcome parameter and will be determined using semi-automated analysis software. CR timing will also be assessed.

Imaging: Functional connectivity in resting state MRI and diffusion tensor imaging (DTI) before and after therapy.

MRI of the skull: The examination takes place in a 3 T scanner (Magnetom Vida, Siemens, Erlangen, Germany, 3 T) at the University Medical Center Essen (Institute for Diagnostic and Interventional Radiology).

Functional imaging–resting-state: fMRI allows indirect measurement of neuronal-related changes in brain metabolic activity (blood oxygenation level-dependent (BOLD) response). The advantages of the method include the recording of the activity of the entire brain in a few seconds, as well as the spatial resolution achieved in the process. During the rs measurement, the participants are not confronted with any tasks or stimulation beyond “lying quietly.”

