Structural recordings: High-resolution, structural, T1-weighted recordings of the brain are required for the analysis of the fMRI data and are acquired using MP-RAGE sampling (or similar T1-weighted methods). Participants have no other tasks to perform during the examinations.

Diffusion tensor imaging (DTI): DTI sequences are applied to investigate structural connectivity in addition to predictors of expectancy effects at the level of functional connectivity. The measurement time for the complete protocol is approximately 30 min.

For the last four items (i.e., experimental computer-based test procedures, biological parameters, eyeblink conditioning, and MRI), the healthy control group is needed as explained in section “Trial design {8}”.

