## Statistical methods

### Statistical methods for primary and secondary outcomes {20a}

Analysis of variance (ANOVA) with repeated measures is planned for the evaluation of the parameters of therapy outcome (questionnaires for depression), therapy expectancy (questionnaires see above), biological parameters, and tests for cerebellar function (neurological examination, ataxia scores, and blink reflex conditioning). In case of missing values, a linear mixed model analysis is planned. An unpaired *T*-test or chi-square test is planned to determine the group differences at a given point in time. Correlation analyses are planned to correlate parameters of therapy success with treatment expectations.

The MRI data will be analyzed using statistical parametric mapping (SPM, https://www.fil.ion.ucl.ac.uk/spm/; last access 8/15/2023): automated group comparisons in terms of *T*-test and ANOVA will be performed including covariates.

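### No planned analysis tests whether the expectancy effect is smaller in patients with cerebellar signs; separately, the method for the once-measured scores and the scope of the healthy controls are each stated inconsistently

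*Protocol article*

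**What the plan says.** **The hypothesis.** Objectives {7} expects mild cerebellar symptoms or limited acquisition of conditioned blinks, which "can be detected in a subset of patients". It continues: "Our hypothesis is that the expectancy effect is less pronounced in this group of patients". No cut-off and no expected share are given.

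**The analyses.** Section {20b} reads "No subgroup analyses are planned". Section {20a} plans:
- repeated-measures ANOVA, with a linear mixed model if values are missing;
- an unpaired t-test or chi-square test for group differences at one time point;
- correlations between therapy success and treatment expectations;
- SPM group comparisons with covariates that are not named.

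The repeated-measures list includes "tests for cerebellar function (neurological examination, ataxia scores, and blink reflex conditioning".

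**The schedule.** Secondary outcomes has "Parameters indicative of cerebellar dysfunction: survey at one time point before therapy (neurological examination and ataxia scores, see below". Eyeblink conditioning follows, with acquisition as its focus and incidence of conditioned responses (CR incidence) as its main parameter.

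**The healthy controls.** Trial design {8} describes them as a "control only for the additional experimental investigations, which is the MRI part and the eyeblink conditioning". The end of Secondary outcomes says instead: "For the last four items (i.e., experimental computer-based test procedures, biological parameters, eyeblink conditioning, and MRI), the healthy control group is needed", and refers back to Trial design for the explanation.

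**The concern.** A claim that an effect is weaker in one kind of patient compares two effects. It needs an interaction term or a comparison of subsets. The protocol states such a claim, declines subgroup analyses, and names nothing else that would do the job. This is more than a detail left to an analysis plan: a later plan that added a subset analysis would contradict {20b}.

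The other two points are separate. A score taken once has no repeated factor, so the method named for the neurological examination and ataxia scores does not fit their schedule. And whether the controls give blood and saliva and do the computer tasks depends on which section the team follows. That matters during recruitment, because measurements not taken then may not be recoverable.

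**Working it through.** **1. The plan's own figure.** Sample size {14} gives 7 per group from d = 0.79 to 1.6 (repeated-measures ANOVA, four time points, two groups, alpha 0.05, power 0.95). For the group-by-time test, lambda = f² × N × m / (1 − rho), with f = d/2 and m = 4. The within-person correlation rho is not stated. With d = 0.79 and an assumed rho = 0.5:
- 7 per group: lambda = 0.395² × 14 × 4 / 0.5 = 17.5, power 0.929;
- 8 per group: power 0.961.

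Rho = 0.3 needs 11 per group and rho = 0.7 needs 5, so the stated 7 is reproduced within the uncertainty about rho. It concerns the main comparison. The protocol gives no sizing for the cerebellar hypothesis.

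**2. Matching each planned analysis to the hypothesis.**

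| Planned analysis | Relates cerebellar status to the size of the expectancy effect? |
|---|---|
| Repeated-measures ANOVA or mixed model | No cerebellar-by-group term named |
| t-test or chi-square at one time point | No; compares levels between groups |
| Correlation of therapy success with expectations | No; cerebellar measures not involved |
| SPM group comparisons with covariates | Not stated; covariates unnamed |
| Subgroup analyses | None planned |

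The expectancy effect could mean the effect of the randomised intervention, since {6b} says expectation is manipulated rather than merely recorded. It could also mean the association of expectation with outcome. Under either reading, a weaker effect in a subset needs an interaction.

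**3. Precision with a binary subset.** n = 30 per arm (Trial design {8}); the share p is an assumption.

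SE = sqrt(2/(np) + 2/(n(1 − p))) in SD units. Detectable difference at two-sided 5% and 80% power = (1.960 + 0.842) × SE.

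| Assumed share p | Subset per arm | SE | Detectable difference | Power for a 0.79 SD difference |
|---|---|---|---|---|
| 10% | 3 | 0.861 | 2.41 SD | 15% |
| 20% | 6 | 0.645 | 1.81 SD | 23% |
| 30% | 9 | 0.563 | 1.58 SD | 29% |
| 50% | 15 | 0.516 | 1.45 SD | 33% |

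If the intervention helped the remaining patients by 0.79 SD and did nothing in the subset, the difference would be 0.79 SD. Detecting that with 80% power would need about 559, 315, 240 or 202 patients in total.

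**4. Precision with a continuous moderator.** For one standardised measure, the slope in each arm has variance of about 1/30. SE of the difference in slopes = sqrt(2/30) = 0.258, and 2.802 × 0.258 = 0.72 SD per SD of the moderator. Between patients one SD above and one SD below the mean, that is 2 × 0.72 = about 1.45 SD.

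**5. Effect of baseline adjustment.** The figures above are unadjusted. If baseline correlates r = 0.5 with T4 (assumed), multiply by sqrt(1 − 0.25) = 0.866: 1.45 becomes 1.25, and 0.72 becomes 0.63.

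**6. Controls, side by side.** MRI and eyeblink conditioning appear in both sections. Computer tasks and biological parameters appear only in Secondary outcomes, while Trial design restricts the controls to the first two.

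**The case against.** The strongest reply is that the gap is narrow and concerns a secondary goal. Much of that is right.

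- A reader might infer that the cerebellar hypothesis cannot be tested at all. The documents do not support this. Whether impairment is present can be examined with the single-time-point tests in {20a}, and for eyeblink conditioning against the healthy controls. Moderation by a continuous score is not barred by {20b}; it is only unplanned.
- A reader might take {20a} to offer nothing but repeated-measures ANOVA. It also plans t-tests and chi-square tests, mixed models and correlations. The once-measured scores therefore have a suitable test in the same paragraph, and their listing under ANOVA is a drafting slip. That slip is not why moderation goes untested.
- Repeated-measures ANOVA is not wrong for eyeblink data. Acquisition over blocks within one session is a repeated measurement; only the factor is unnamed.
- A reader might infer that cortisol response or connectivity will be correlated with outcome and misread as predicting the expectancy effect. No such correlation is planned, the predictor search is labelled exploratory, and its model terms may properly sit in a fuller document.
- Following Trial design would not leave inflammatory markers without any comparison. Change from T1 to T4 and the contrast between arms remain; only a comparison with healthy values is lost.

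What the reply does not remove is that the modification hypothesis has no planned analysis, the once-measured scores are given a repeated-measures method, and the two sections disagree on the controls.

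**Conclusion.** The point holds in limited form. The hypothesis of a smaller expectancy effect in a cerebellar subset is stated, subgroup analyses are declined, and no listed analysis answers it. The mismatch for the neurological and ataxia scores and the conflict over the controls are separate and also stand.

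The numbers support calling any such test exploratory. At the most favourable split (50%) the detectable difference of 1.45 SD is near the top of the 0.79 to 1.6 range on which sizing was based, and the protocol expects its own effect to be lower. Quoting 1.45 SD alone would be tempting but wrong: the protocol says only that a subset is affected, and smaller shares raise the figure to as much as 2.41 SD at 10%. The continuous figure of 0.72 SD per SD is the one that matches the proposed model.

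All figures assume 30 analysed patients per arm, the same subset share in both arms, normal approximations and no baseline adjustment. The continuous figure is for one moderator; two correlated moderators fitted together would do less well.

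**What to change.** 1. **{20b}:** state one exploratory analysis. To a baseline-adjusted model of T4 depression, add the baseline cerebellar measures (CR incidence and the ataxia score, both continuous) and their interactions with randomised group. Report each interaction with its 95% CI and label it exploratory. Continuous measures avoid a cut-off that the protocol does not define. Reword the sentence on subgroup analyses to agree.
2. **{20a}:** move the neurological examination and ataxia scores to the t-test or chi-square test already planned for a single time point. For CR incidence, compare patients with healthy controls and name conditioning block as the within-subject factor.
3. **Trial design {8} and Secondary outcomes:** reconcile which measures the controls provide. Neither list names the neurological examination or ataxia scores for controls, so say whether they are included.

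**Cost:** wording and a little extra analysis. Power for the interaction will be low, so a wide interval is likely and must not be read as absence of modification. If the controls follow Secondary outcomes, they also give blood and saliva and do the computer tasks, which that section already foresees.

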### Methods in analysis to handle protocol non-adherence and any statistical methods to handle missing data {20c}

Linear mixed model analyses are planned in case of missing values.

### Plans to give access to the full protocol, participant-level data, and statistical code {31c}

There are no plans for granting public access during the run-up to publication. The datasets analyzed during the current study and statistical code are available from the corresponding author on reasonable request, as is the full protocol.

### Oversight and monitoring

#### Composition of the coordinating center and trial steering committee {5d}

This is a monocentric, investigator-initiated study. The coordinating center is the LVR-University-Hospital Essen. The daily local organization and coordination of the study are ensured by [name] [name] (KMS), who obtains informed consent as the clinic’s physician. [name]. [name] (KK) and [name]. [name] (DT) supervise the study. Meetings are held regularly every 3 months as part of the in-house research conference and at short notice to clarify questions and problems that may arise. There is no Stakeholder and Public Involvement Group (SPIG).

#### Composition of the data monitoring committee, its role, and reporting structure {21a}

This is a monocentric, investigator-initiated study. No data monitoring committee was required by the local Ethics Committee as this is a low-risk intervention.

#### Frequency and plans for auditing trial conduct {23}

As this is a very low-risk intervention, there are no explicit audits, but there is a regular exchange based on the initiative of the Trial Steering Group with the local ethics committee regarding the status of the study. Meetings of the Project Management Group and the Trial Steering Group are held regularly every 3 months as part of the in-house research conference and at short notice to clarify questions and problems that may arise.

#### Plans for communicating important protocol amendments to relevant parties (e.g., trial participants, ethical committees) {25}

In case of changes to the study protocol, these are submitted to the local ethics committee in the form of an official amendment and reported to the German Registry of Clinical Trials (DRKS; https://www.drks.de/drks_web/; last access 8/15/2023).

#### Dissemination plans {31a}

Publication of the results of the study in a peer-reviewed journal as well as the presentation of posters or talks on the (preliminary) outcomes are planned. There are no publication restrictions.

## Discussion

The aim of the present study is to investigate the influence of the expectations of patients with therapy-resistant depression on the treatment with TMS. The therapy success will be objectified by cognitive instruments and biological parameters in addition to instruments of self- and external assessment of depressive symptoms. Furthermore, the neuronal networks relevant to therapy expectancy will be investigated in order to understand underlying mechanisms more closely and to be able to optimize the possibilities of a well-tolerated non-invasive treatment in the long term. In particular, the role of the cerebellum will be investigated, as it might contribute to treatment expectations. For the evaluation of cerebellar function, eyeblink conditioning will be used in addition to a clinical examination. In eyeblink conditioning, the ability to predict future events is central for learning to occur and depends on the integrity of the cerebellum.

Using analysis of functional connectivity with rs data, predictors of the expectancy effect will be identified. It is known from the literature that these overlap with predictors of treatment response as well as stimulation targets of treatment of depression by TMS or DBS [12].

Thus, the present study aims at contributing to the question to what extent the effect of treatment of MDD by noninvasive stimulation can be separated from an influence on treatment expectation in general, in terms of the placebo effect. This could be the starting point for a deeper understanding of the pathophysiology of depressive disorder. Conversely, the principle of enhancing expectancy effects by noninvasive stimulation could be transferable to other disease patterns.

A weakness of this study may be the low case number. For our power calculation, studies investigating treatment expectancy in other disorders [46] were considered in addition to the above-mentioned study by Claus et al. [7], who investigated a psychological intervention in addition to antidepressant medication. In particular, the generally low effect sizes of antidepressant treatments [47] could be problematic here.

Another difficulty is certainly the complex and in part very extensive study protocol, which not only might limit the number of study participants but can also amount to a considerable effort for patients suffering from depressive disorder. In order to accommodate the study participants, it is possible to distribute the examinations planned before the start of the study over several appointments. Nevertheless, this aspect, as well as the high frequency of treatment days, could discourage participants with long travel distances from participating in the study.

Despite this, the study offers the possibility to increase the availability of treatment with TMS, a comparatively new and not yet widely introduced treatment for therapy-resistant depression, also on an outpatient basis. Furthermore, the study should contribute to the understanding and treatment optimization of an individually very disabling and economically highly relevant disease.

## Trial status

This is the first version of the study protocol (2022/07/01). Recruitment started in June 2022 with the goal of completing recruitment by November 2023.

## Data Availability

After publication in a peer-reviewed journal, the dataset will be made available to other scientists upon personal request and justified intention.

## Abbreviations

AE: Adverse events
BDI: Beck depression inventory
CAR: Cortisol awakening response
CRP: C-reactive protein
DBS: Deep brain stimulation
DMN: Default mode network
DRKS: German Registry of Clinical Studies
DTI: Diffusion tensor imaging
EU-DSGVO: European Data Protection Regulation
(f)MRI: (Functional) magnetic resonance imaging
HDRS: Hamilton Rating Scale for Depression
IL-6: Interleukin 6
MDD: Major depressive disorder
(r)TMS: (Repetitive) transcranial magnetic stimulation
RS: Resting state
TNFα: Tumor necrosis factor α
